### Diet module (‘Diet Tips’)

The diet module consists of a 6-week intervention containing written information and audio tracks designed specifically for this study, considering the best available evidence,^64^,^66^ and is complemented with links to online, readily available resources. The diet module provides information about the basics of nutrition, including food groups, ultra-processed foods, the impact of sugar on health and the role of antioxidants. Participants will be offered weekly tasks on how to read nutrition labels, make healthier food choices and use a healthy diet as a coping strategy to self-manage their chronic pain. The content is strictly educational, encouraging participants to adopt healthier eating habits. No recommendations will be made regarding specific diets, and no meal plans or recipes to follow will be provided. Every week, new content will be made available (ie, unlocked) and participants will be recommended to complete the weekly content at their convenience. Completing the diet module should take approximately 10–30 min per week for 6 weeks.

### Automated push notifications

Participants will receive lifestyle-based, self-management push notifications providing encouragement, advice and motivation. The content will cover education about LBP, and tips about exercise, physical activity, sleep, diet, mood and use of care and medication, aiming at improving self-care and pain coping strategies, as well as promoting engagement with the app. Each notification will be approximately 160 characters in length and will include the name of the app. Some will also include the participant’s preferred contact name. Participants will receive up to four notifications per week for 6 weeks in random time slots at 09:00, 12:30, 16:00 and 18:00. There will be no distinction among intervention groups.

The content of the push notifications has been adapted from the TEXT4MyBACK trial,^34^ where a bank of text messages was developed for people with LBP. The messages were co-designed by consumer representatives from Musculoskeletal Health Australia, multidisciplinary clinicians and experts, considering the best available evidence,^1516 32 67^,^71^ and incorporating concepts from the behaviour change model,^72^ as described elsewhere.^34^ Key domains were defined based on the ‘Managing Your Pain: An A-Z Guide’,^73^ developed and published by Musculoskeletal Health Australia. The frequency of the push notifications was also established based on previous research.^34 74^

### Study arms

This MAMS trial will comprise five study arms, including one control group and four intervention groups. All participants will receive access to the My Back Exercise app. However, access to specific components within the app will be available according to the participant’s allocation, as described next and illustrated in figure 1. Recruitment and enrolment will commence at the same time for all study arms, and there will be no introduction of new arms into the study. No specific recommendations will be made regarding concomitant care during the trial.

**Figure 1 F1:**
[figure not shown]
Consolidated Standards of Reporting Trials flow chart. PCF, Participant Consent Form; PIS, Participant Information Statement; QR, quick response.

Control group: education module alone.Intervention group 1: education module + educational notifications + exercise module.Intervention group 2: education module + educational notifications + exercise module + sleep module.Intervention group 3: education module + educational notifications + exercise module + diet module.Intervention group 4: education module + educational notifications + exercise module + sleep module + diet module.

All participants will have access to specific components of the app (according to their group allocation) during the entire study (ie, 1 year after the last recruited participant completes the intervention period). After this period, offline access to the full content of the app will be offered to all participants in the study for an additional 6 weeks.

### Monitoring adherence to the intervention

To measure adherence to the intervention, participants will complete a self-reported activity tracker within the My Back Exercise app for the exercise and sleep modules (which offer tailored content), and a weekly electronic logbook via REDCap for the education and diet modules. The invitation to complete the weekly electronic logbook will be sent via scheduled and automated emails via REDCap. Additionally, app use and engagement (eg, frequency of use, time spent, content accessed) will be collected in a de-identified format using data analytics, drawn from the app’s backend system via the Matomo web analytics platform.^75^ At 6 and 9 months after randomisation, there will also be a brief phone call with the participants to follow-up on adherence and engagement with the app. Adherence will be calculated for each study arm and the entire study.

For the exercise module, participants will be recommended to complete at least three exercise sessions per week, totalling 18 sessions over the 6-week exercise programme. Data will be drawn primarily from the app’s self-reported daily activity tracker, and additional insights will be provided by data analytics from Matomo.^75^ Adherence levels will be assessed based on the proportion of self-reported completed exercise sessions relative to the number of recommended sessions and categorised as low (0%–35%, or up to six exercise sessions completed), moderate (35%–70%, or 7–12 exercise sessions completed) and high (70%–100%, or 13–18 exercise sessions completed). Adherence will be considered acceptable when participants complete at least 70% of their prescribed exercise programme.^76^

For the sleep module, participants may choose weekly or daily goals over the 4-week sleep programme. Data will be drawn primarily from the app’s self-reported daily or weekly activity tracker according to the goal selected by the participant, and additional insights will be provided by data analytics from Matomo.^75^ Adherence levels will be assessed based on the proportion of self-reported completed goals relative to the number of recommended goals and categorised as low (0%–35%), moderate (35%–70%) and high (70%–100%). Adherence will be considered acceptable when participants complete at least 70% of their prescribed sleep programme.

For the education and diet components, participants will be recommended six structured modules over the 6-week app programme. Data will be drawn primarily from the weekly electronic logbooks, categorised as ‘not started’, ‘partially completed’ or ‘completed’, and additional insights will be provided by data analytics from Matomo.^75^ Adherence levels will be assessed based on the number of self-reported completed modules and categorised as low (0%–35%, or up to two modules completed), moderate (35%–70%, or three to four modules completed) and high (70%–100%, or five to six modules completed). Adherence will be considered acceptable when participants complete at least 70% of their prescribed education or diet programmes.

A planned exploratory analysis will be conducted to investigate the potential impact of adherence on the magnitude of the treatment effects.

### Outcomes

#### Primary outcome

The primary outcome measure will be self-reported physical function, measured by the PSFS^56 77^ at baseline, 6, 12 and 52 weeks after randomisation. The primary time-point is 6 weeks after randomisation (ie, immediate post-intervention), while the secondary time-points are 12 and 52 weeks after randomisation. The PSFS, originally proposed by Stratford *et al*,^77^ is a valid, reliable and responsive self-report instrument^56^ designed to assess functional change in people with musculoskeletal disorders. Participants identify three important activities they are unable to do or have difficulty with because of their LBP and rate their ability to perform each activity. Each activity is rated on an 11-point numerical rating scale ranging from 0=‘unable to perform activity’ to 10=‘able to perform the activity at preinjury level’. The total score, calculated by summing the numerical ratings for each activity, is provided on a discrete scale ranging from 0 to 30, where higher scores indicate better function.

#### Secondary outcomes

Secondary outcome measures will be grouped into domains and will include:

Symptoms and function:

Pain intensity, measured by the Numeric Rating Scale (NRS)^78^ at baseline, 6, 12 and 52 weeks after randomisation.Pain frequency, measured by a self-reported question at baseline, 6, 12 and 52 weeks after randomisation.Disability, measured by the Roland-Morris Disability Questionnaire (RMDQ)^56 79^ at baseline, 6, 12 and 52 weeks after randomisation.

Quality of life and general health:

Health-related quality of life (HRQoL), measured by the EuroQol 5-Dimension 5-Level (EQ-5D-5L)^80^ at baseline, 6, 12 and 52 weeks after randomisation.Sleep quality, measured by the Pittsburgh Sleep Quality Index (PSQI)^81 82^ at baseline, 6, 12 and 52 weeks after randomisation.Consumption of highly processed food, measured by the Short Screening Questionnaire of Highly Processed Food Consumption (sQ-HPF)^64^ at baseline, 6, 12 and 52 weeks after randomisation.

Health behaviours and beliefs:

Exercise importance, measured by a self-reported question at baseline and 6 weeks after randomisation. Participants indicate how important it is to them to do regular exercise to manage their back condition. Answer options are presented on a 7-point Likert-type scale ranging from 1=‘not at all important’ to 7=‘extremely important’, where higher scores indicate higher importance.Exercise self-efficacy, measured by the Self-Efficacy for Exercise (SEE) Scale^83^ at baseline, 6, 12 and 52 weeks after randomisation.Adherence to exercise recommendations, measured by the Exercise Adherence Rating Scale (EARS)^84^ at 6 weeks after randomisation.

Healthcare utilisation and engagement:

Co-intervention use, measured by a self-reported questionnaire specifically designed for this study at baseline, 6, 12 and 52 weeks after randomisation.Health literacy level, measured by the Health Literacy Questionnaire (HLQ)^85^ at baseline, 6, 12 and 52 weeks after randomisation.

Patient perception of change:

Global perceived effect, measured by the Global Perceived Effect (GPE) scale^86^ at 6, 12 and 52 weeks after randomisation.Impression of change in overall status, measured by the Patient’s Global Impression of Change (PGIC)^87^ at 6, 12 and 52 weeks after randomisation.

Satisfaction and usability of the app:

Overall satisfaction, measured by a self-reported question at 6 weeks after randomisation. Participants indicate how satisfied they are with the electronic resources they accessed as part of this study. The question is rated on a 7-point Likert-type scale ranging from 1=‘very dissatisfied’ to 7=‘very satisfied’, where higher scores indicate higher satisfaction.Usefulness of the app, measured by self-reported questions at 6 and 52 weeks after randomisation. Participants will be asked to rate how useful they found the My Back Exercise app, overall and in each module. Answer options are presented on a 7-point Likert-type scale ranging from 1=‘completely useless’ to 7=‘extremely useful’, where higher scores indicate the app or the modules were perceived to be more useful.Frequency of the push notifications, measured by self-reported questions at 6 and 52 weeks after randomisation in the intervention groups only. Participants indicate whether the number of notifications received over the past 6 weeks was the right amount for them. Answer options are presented on a 7-point Likert-type scale ranging from 1=‘strongly disagree’ to 7=‘strongly agree’, where higher scores indicate higher agreement. Participants who select ≤3 will be further asked whether they received 1=‘too few’ or 2=‘too many’.

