### Sleep module (‘Sleep Tips’)

The sleep module consists of a 4-week tailored sleep educational programme containing written information and audio tracks designed specifically for this study, with advice from expert researchers in the sleep field, considering the best available evidence.^62 63^ The sleep module provides information about sleeping habits, sleep efficiency and how sleep and LBP are connected. Participants will learn how they can optimise their sleep, and they will be given hints, tips and personalised goals on how to improve their sleeping habits through breathing and relaxation training and stimulus control strategies. Once a week, participants will be asked to review sleep information and select a goal for the week. Based on the goal selected, participants will receive daily or weekly reminders to work on their goal. The reminder will be a push notification at an appropriate time of the day (ie, 08:00 for a daytime tip and 20:00 for an evening tip). Completing the sleep module should take approximately 10–15 min per week for 4 weeks.

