**Figure 2 F2:**
[figure not shown]
Multi-arm multi-stage design.

**Table 1 T1:** Study visits and procedures schedule

Procedures	Study period and timepoints						
	Screening and Enrolment	Baseline	Allocation	Intervention	Follow-up data collection		
	Week −4 to −1	Week 0	Week 0	Week 1 to 6	Week 6	Week 12	Week 52
Screening and Enrolment							
Informed consent	X						
Eligibility screening	X						
Baseline assessment		X					
Allocation			X				
Interventions							
Control group			X	X	X	X	X
Intervention groups			X	X	X	X	X
Measures							
General characteristics		X					
Primary outcome							
Physical function		X			X	X	X
Secondary outcomes							
Pain intensity		X			X	X	X
Pain frequency		X			X	X	X
Disability		X			X	X	X
Quality of life		X			X	X	X
Sleep quality		X			X	X	X
Consumption of HPF		X			X	X	X
Exercise importance		X			X		
Exercise self-efficacy		X			X	X	X
Adherence to exercise					X		
Co-intervention use		X			X	X	X
Health literacy level		X			X	X	X
Global perceived effect					X	X	X
Impression of change					X	X	X
Overall satisfaction					X		
Usefulness of the app					X		X
Push notifications frequency					X		X
Process measures							
Conversion rate		X					
Recruitment rate					X		
Rate of completed follow-up					X	X	X
Other measures							
Smallest worthwhile effect		X					
Adverse events				X	X		X

X indicates the timepoint(s) when each study procedure will occur.

HPF, highly processed food.

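### The week-52 question on push-notification frequency asks about a six-week window in which no notification is scheduled

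*Protocol article*

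**What the plan says.** All references are to the protocol article.

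- **Outcomes, Secondary outcomes (satisfaction and usability of the app)** sets the times and the population: "Frequency of the push notifications, measured by self-reported questions at 6 and 52 weeks after randomisation in the intervention groups only". The item is described once, for both times: "Participants indicate whether the number of notifications received over the past 6 weeks was the right amount for them". It is scored from 1 to 7 for agreement, and low scorers get a follow-up: "Participants who select ≤3 will be further asked whether they received 1=‘too few’ or 2=‘too many".
- **Table 1** has a row "Push notifications frequency", marked at weeks 6 and 52.
- **Automated push notifications** gives the schedule: "Participants will receive up to four notifications per week for 6 weeks in random time slots". It adds: "There will be no distinction among intervention groups".
- **Sleep module** describes a 4-week programme and says: "Based on the goal selected, participants will receive daily or weekly reminders to work on their goal". It states that these reminders are themselves push notifications.
- **Study arms** gives the sleep module to intervention groups 2 and 4 only. It keeps the allocated app components open to participants for the whole study, as does **Ancillary and post-trial care**.

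**The concern.** A question with a fixed recall window measures something only if the exposure falls inside that window. At week 6 the window and the notification period coincide. At week 52 the same window looks back over a stretch in which the article schedules no notifications.

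A participant answering at week 52 can rate an amount of zero, or can ignore the stated window and recall a programme that ended most of a year before. The analyst cannot tell which was done. Anyone scoring 3 or lower is then asked to choose between too few and too many, which has no clear meaning when nothing was due to be sent. The week-52 result of a declared secondary outcome would be reported without a known referent.

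There is a smaller question at week 6. Groups 2 and 4 receive two kinds of push message, and the item as described does not say which kind it is about.

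**Working it through.** The plan gives no figure of its own to reproduce. The check compares time windows and then counts messages.

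**Inputs**
- Assessment times: T = 6 and T = 52 weeks after randomisation (Secondary outcomes; Table 1).
- Recall window: T − 6 to T (Secondary outcomes).
- Educational notifications: 6 weeks, at most 4 per week (Automated push notifications).
- Sleep reminders: a 4-week module, daily or weekly according to the goal chosen (Sleep module).
- Start of programme: after the app is installed, hence d weeks after randomisation (Randomisation section). The article gives no value for d. I assume 0 to 4 weeks.

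**Window overlap**

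Notifications run from week d to week d + 6. Overlap = max(0, min(T, d + 6) − max(T − 6, d)).

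| d (weeks, assumed) | Overlap at week 6 | Overlap at week 52 |
|---|---|---|
| 0 | 6 | 0 |
| 1 | 5 | 0 |
| 2 | 4 | 0 |
| 3 | 3 | 0 |
| 4 | 2 | 0 |

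At week 52 the window opens at 52 − 6 = 46. With d = 0, scheduled sending ended at week 6, a gap of 46 − 6 = 40 weeks. Any overlap would need d + 6 > 46, that is, a start more than 40 weeks after randomisation. The sleep module is shorter (4 weeks), so its reminders, if the module starts with the programme, do not reach the window either.

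**Message counts by the end of the programme**

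These are ceilings. They assume one sleep reminder per day or per week and the same type of goal in all four weeks; the article states neither.

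- Groups 1 and 3: 4 × 6 = 24.
- Groups 2 and 4, weekly goals: 24 + 1 × 4 = 28, of which 4/28 = 14% are sleep reminders.
- Groups 2 and 4, daily goals: 24 + 7 × 4 = 52, of which 28/52 = 54% are sleep reminders.

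**Tally**

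Four intervention arms at two times make 8 cells. In 4 (all arms at week 52) nothing is scheduled in the window. In 2 (groups 2 and 4 at week 6) two kinds of message may be mixed. In 2 (groups 1 and 3 at week 6) the item works as intended.

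**The case against.** **Notifications might continue.** App components stay open throughout the study, and Table 1 marks the interventions at weeks 12 and 52. But continued access is not continued sending. The notification section states a 6-week limit and no passage extends it. If sending does go on, that section is the one in error, so the passages need reconciling either way.

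**The form is not shown.** The article paraphrases the items, and the questionnaire may be worded differently. This carries real weight for week 6: the form may already name the type of message, and the article calls the sleep messages reminders while the arm definitions speak of educational notifications. It carries less for week 52, where the article itself states both the times and the window.

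**Stronger readings a reader might infer, which the documents do not support**
- *The outcome as a whole cannot show whether the frequency was right.* At week 6 the window matches the notification period, apart from any installation delay, and no other push message is described for groups 1 and 3. The item can answer its question there.
- *Week-52 answers would drift towards too few.* A participant content to receive none could agree that the amount was right and would never see the follow-up. No direction can be inferred.
- *Sleep reminders contradict the statement that intervention groups do not differ.* That sentence concerns the educational notifications only; there is no conflict.
- *Groups 2 and 4 carry a known multiple of the load in groups 1 and 3.* The counts are ceilings resting on assumptions, so no ratio should be quoted as a range.
- *A pooled figure would mislead.* Nothing in the article says that the arms will be pooled on this item.

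**Conclusion.** The point holds for the week-52 administration. As written, the recall window contains 0 weeks of scheduled notifications in every intervention arm, so the week-52 result is uninterpretable. This rests on the 6-week sending limit being correct and on the item being used at week 52 as described. It is not sensitive to the start delay within the assumed 0 to 4 weeks, or indeed up to 40 weeks.

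The week-6 point is minor and conditional on the form matching the article's description. If it does, an answer from groups 2 or 4 cannot be attributed with certainty to the educational notifications.

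Severity is low. This is a descriptive usability outcome that the control group is not asked. It does not enter the primary analysis of physical function, the sample size or the rules for dropping arms at the interim analysis.

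**What to change.** 1. Delete the week-52 administration of this item from Secondary outcomes and from Table 1, or reword it at week 52 so that it refers to the 6-week programme. If notifications are in fact sent after week 6, correct the section on automated push notifications instead, so that the three places agree.
2. At week 6, name the educational notifications in the item. If views on the sleep-goal reminders are also wanted, ask about them in a separate line for groups 2 and 4.
3. Report answers already collected under the present wording separately from later ones. Recruitment began in June 2024, so the first week-52 assessments fall due from about June 2025 and some may already be in hand.

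The cost is an edit to one REDCap item, one change to Table 1, and the ethics submission that the article requires for any protocol change. Deleting the week-52 item slightly reduces participant burden. Rewording it keeps a week-52 result, but one that depends on recall of a programme long finished. No effectiveness analysis changes.

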#### Process measures

Conversion rate, measured using data analytics (ie, audit of study-specific screening and enrolment logs) at baseline. The number and percentage of participants screened who proceed to enrol in the clinical trial will be calculated.Recruitment rate, measured using data analytics (ie, audit of study-specific screening and enrolment logs) at 6 weeks after randomisation. The average number and percentages of participants enrolled in the study per month and per day of active recruitment will be calculated.Rate of completed follow-up, measured using data analytics (ie, audit of study-specific database) at 6, 12 and 52 weeks after randomisation. The number and percentage of participants enrolled in the study who completed the follow-up assessment will be calculated.

#### Other measures

Smallest Worthwhile Effect^88^ in function, measured at baseline. Participants will be asked to nominate the smallest score in the PSFS (total and for each activity) they would need to achieve to consider the costs, risks and inconveniences of using a mobile application intervention worthwhile.Adverse events, collected through a self-reported form at 2, 4, 6 and 52 weeks after randomisation.

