### Harms

An adverse event is defined as any undesirable, unfavourable or unintended sign, symptom or disease experienced by a participant in the course of clinical research, which does not necessarily have a causal relationship with the study interventions. A serious adverse event is defined as an unforeseen medical event that occurs in the course of clinical research that results in the participant’s death, is life-threatening to the participant, requires the inpatient hospitalisation or prolongation of existing hospitalisation, or leads to the participant having a persistent or significant disability/incapacity.^91^ This study has been designed to minimise or prevent potential risks. Nevertheless, adverse events are expected and may include flare-ups of LBP, exercise-induced muscle pain, soreness and cramps, unexpected trips and falls, and additional treatments sought for LBP.

Fortnightly, participants will be prompted by email to report the occurrence of adverse events through an Adverse Events Report Form via REDCap during the 6 weeks of intervention and, again, at 52 weeks after randomisation. Participants will indicate any changes in their condition, and the research team will evaluate whether it was related to the intervention or not. When appropriate, participants will be asked to provide further information on whether the adverse event persisted for more than 24 hours and whether medical attention was sought. Participants will be encouraged to contact the research team if they have ongoing or unresolved concerns about the adverse event and its relationship with the study interventions. The research team will monitor reported adverse events until their resolution. Potential harms resulting from participation in the study will not incur any special compensation arrangements. The type of adverse event and the proportions of participants experiencing each event will be reported.

Serious adverse events will be recorded and reported to the Human Research Ethics Committee (HREC) and study sponsor, in accordance with relevant regulatory standards.

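### Adverse events are solicited at weeks 2, 4 and 6 and then not until week 52, although follow-up contacts already exist at week 12 and at 6 and 9 months

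*Protocol article*

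**What the plan says.** Other measures sets the collection times: "Adverse events, collected through a self-reported form at 2, 4, 6 and 52 weeks after randomisation". Harms describes the same plan. For the programme period it states "Fortnightly, participants will be prompted by email to report the occurrence of adverse events through an Adverse Events Report Form via REDCap", and the timing is given as "during the 6 weeks of intervention and, again, at 52 weeks after randomisation". Table 1 marks adverse events in the columns for weeks 1 to 6, week 6 and week 52, and leaves week 12 empty.

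Other contacts are planned in between. For the primary outcome, week 6 is the main time-point, "while the secondary time-points are 12 and 52 weeks after randomisation", and Table 1 shows most secondary outcomes at week 12 too. Monitoring adherence to the intervention adds: "At 6 and 9 months after randomisation, there will also be a brief phone call with the participants to follow-up on adherence". The calls' other stated purpose is app engagement. That section does not mention harms.

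Exposure does not end at week 6. Under Study arms: "All participants will have access to specific components of the app (according to their group allocation) during the entire study". Ancillary and post-trial care repeats this.

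Between weeks 6 and 52, Harms describes two other routes. One is initiated by the participant: "Participants will be encouraged to contact the research team if they have ongoing or unresolved concerns about the adverse event". The other is the team's follow-up of events already reported, until they resolve. Harms also says that the results will give the types of event and the share of participants with each.

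**The concern.** Solicited reporting is dense for six weeks and then stops for most of a year, while the intervention arms can still use a home-based, unsupervised exercise module. The 6- and 9-month calls about app engagement show that the protocol itself expects continued use.

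Four things are at stake.

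- **Counting.** The events that the protocol expects include flare-ups, soreness, cramps and falls. Many are short-lived, and one follow-up question is whether the event lasted beyond 24 hours. A single self-report many months later suits that detail poorly.
- **Timeliness.** Serious events must go to the ethics committee and the sponsor. With no scheduled question, one that occurs soon after week 6 may reach the team late.
- **Missing data.** Someone who answers at week 12 or takes a call, but misses week 52, contributes no solicited harms data after week 6.
- **Balance.** Week 12 is a stated time-point for benefit and has no harms form alongside it.

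**Working it through.** This is schedule arithmetic. No sample size, power or error rate enters, and the protocol states no gap length to reproduce.

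**Inputs**

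- Adverse-event form: weeks 2, 4, 6 and 52 (Other measures; Harms and Table 1 agree).
- Existing contacts after week 6: the week-12 survey (Primary outcome, Table 1) and calls at 6 and 9 months (Monitoring adherence to the intervention).
- Assumption: 52 weeks = 12 months, so 6 months = 52 × 6/12 = week 26 and 9 months = 52 × 9/12 = week 39.

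**Current schedule**

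Gap = later time minus earlier time, counted from randomisation:

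- 2 − 0 = 2 weeks
- 4 − 2 = 2 weeks
- 6 − 4 = 2 weeks
- 52 − 6 = 46 weeks

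Share of the follow-up year inside the last gap: 46/52 = 88%. Three planned contacts (week 12, about week 26, about week 39) fall within it.

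**If existing contacts carried the question**

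| Times after week 6 with a question | Gaps (weeks) | Longest gap |
|---|---|---|
| 52 (current) | 46 | 46 |
| 12, 52 | 6, 40 | 40 |
| 12, 26, 39, 52 | 6, 14, 13, 13 | 14 |

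Week 12 alone does little for the longest gap. Most of the gain comes from the two calls.

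**What cannot be calculated**

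The documents give no event rate after week 6 and no recall-loss figure, so the size of the under-count is unknown. They allow 15% loss at 6 weeks but give no figure for week 52, so the number of participants with no solicited harms data after week 6 is also unknown.

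**The case against.** The schedule is consistent across three places and has a visible rationale. The structured exercise programme, the notifications and the primary time-point all fall in the first six weeks, when prompts are fortnightly. The recommended number of sessions is defined only for that period. This stands, and it limits the severity. One small qualification is that the form is timed from randomisation, whereas the Randomisation section starts the programme once the app is installed. The week-6 form could therefore reach a late installer before the programme ends.

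A reader might infer that nothing but long recall informs harms after week 6. The documents do not support that. Pain intensity, pain frequency, disability, perceived change and co-intervention use are measured at week 12 in all arms and could show worsening or care-seeking. Participants can contact the team unprompted, and an internal committee meets weekly with adverse events in its remit. These routes narrow the gap, but they are not adverse-event collection, and the week-12 measures would miss falls. The recall window of the week-52 form is also not stated; 46 weeks is the longest it would need to cover.

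A reader might also infer that the calls contain no adverse-event question. The article gives their purpose but not their script, so only the absence of a stated question is established. The week-12 omission is firm, because Table 1 shows it.

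Finally, a change made now alters ascertainment during the trial. Recruitment began in June 2024 and arms may be dropped at the interim analysis, so old and new schedules would be mixed unevenly. A spoken question also differs from a self-completed form. This objection is sound, and the remedy has to deal with it.

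**Conclusion.** The point holds as a weakness in a fixed schedule, of minor to moderate severity. Scheduled adverse-event collection has a 46-week gap, 88% of the follow-up year, during which app access continues and three planned contacts take place with no adverse-event question stated. The likely effects are under-counting of transient events after week 6, possible late knowledge of serious events, no solicited late harms data from participants lost before week 52, and no concurrent harms data for the week-12 benefit results.

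It would go too far to conclude that harms at 12 and 52 weeks cannot be interpreted. Every arm follows the same schedule and events to week 6 are solicited fortnightly, so arms can still be compared. The more exposed figures are the absolute proportions after week 6.

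The verdict assumes that the unseen call script adds no adverse-event question. If it does, the firm part is the blank at week 12, and the article should state what the calls collect. That long recall loses transient events is a judgement; the documents supply no figure for it.

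**What to change.** 1. Add the existing Adverse Events Report Form to the week-12 REDCap survey.
2. Add the same question, in identical wording for all arms, to the 6- and 9-month calls.
3. Update Other measures, Harms and Table 1 to match, including a place in the table for the two calls.
4. Report adverse events separately for the period to week 6 and the period after it. Compare arms after week 6 only among participants followed under the same collection schedule, and record which schedule each participant had.

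The cost is a form that is already built, one scripted question, a few minutes of participant time and a minor ethics amendment. No new contact is needed. The lasting cost is statistical: participants enrolled earlier, and possibly those in dropped arms, will have been followed at least partly on the old schedule, which shrinks the group available for the later comparison. Step 4 contains that problem but does not remove it.
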